## Methods: assignment of intervention

### Allocation and blinding

We will use Castor EDC for the online measurements and for randomisation of the participants [48]. Castor EDC uses a variable block randomisation method and randomly assigns participants to one of the two groups, the allocation ratio will be 1:1. The randomisation sequence is masked for study personnel. In order to balance the size of the intervention and usual care groups in each region, randomisation will be stratified according to regions (Amsterdam or Nijmegen). Patients will be included in either the intervention group or the usual care group based on the random allocation. The research assistant will give all patients a unique patient identification number, matching with the corresponding name to inform each participant about the allocation. All patients will be informed about the allocation by the research assistant by regular mail. Patients randomised to the psychosomatic therapy group will also be informed about the psychosomatic therapy by telephone by the research assistant and will receive a referral from their GP to one of the psychosomatic therapists participating in this study. If patients are randomised to the usual care group, they will be offered to receive psychosomatic therapy after completion of the study if still indicated. The research assistant will inform all GPs about the inclusion and allocation of their patients by regular mail or secure e-mail.

Since psychosomatic therapy is a face-to-face intervention, patients and therapists cannot be blinded to allocation. The data analysts will not be blinded to treatment assingments, as this would be unfeasible because they are also involved in data collection.

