### Outcome measures

#### Primary outcome

In order to estimate the primary outcome of the treatment we will measure patients’ level of specific functioning and disability measured with the PSFS. The PSFS is a self-reported, thoroughly validated, responsive measurement instrument for up to three individual activities for which patients perceive limitations rated on an 11-point numeric rating scale (NRS) ranging from 0–10 (0 representing ’impossible‘ and 10 ’not a problem at all‘) [24, 31–33]. We will measure mean change from baseline at 4 and 12 months’ follow-ups.

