## Methods: data collection, management and analysis

### Data collection

#### Data collection randomised trial

Data will be collected and stored digitally using Castor EDC [48]. Castor EDC is a Cloud-based Electronic Data Capture platform that enables easily capture of our data. Castor EDC is fully compliant with Good Clinical Practice, maintains stringent data security procedures and provides an audit trail. We will develop a case record form (electronic document designed to record all the information for an individual study subject), build a database, define a procedure for data entry, define and programme validation checks to ensure the consistency of the dataset, and set up the randomisation procedure, web questionnaire and/or logistic module. We will check for data-entry errors and range checks in values weekly to improve data quality during data collection. The participants will receive an e-mail with a link for all baseline and follow-up measurements, and if necessary, a reminder, to complete the measurements online. If participants still fail to respond, an independent research assistant will call them to encourage them to fill out the questionnaires. In case participants prefer a paper version, the measurements will be send by regular mail.

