A strength of our study is that the psychosomatic therapy is a well-accessible intervention already delivered in primary care by physical therapists with special interests in MUS. Psychosomatic therapy has an integral approach, focussing on physical, psychological and psychosocial factors; therefore, the intervention is possibly more appropriate for patients who decline CBT. Furthermore, the guideline on the management of MUS of the Dutch College of General Practitioners [30] is very positive about psychosomatic therapy, although the evidence for the effectiveness of this therapy is still lacking. All participating psychosomatic therapists will participate in an intensive training (e-learning and meetings) about the content of the standardised treatment protocol and education in MUS. By this training we will minimise the differences in the psychosomatic therapy delivered by the psychosomatic therapists [66]. In addition, we will conduct a process evaluation through interviews with the participating therapists to explore the possible facilitators and barriers of the psychosomatic therapy from the therapists’ perspective. The findings will improve or refine the intervention. Another strength of our study is the 12-month follow-up measurement as it will result in data being obtained about long-term (cost)-effectiveness of the intervention. The aim of the psychosomatic therapy is to give patients insight into the interaction of their psychosocial factors with their somatic complaints and thus to empower patients to regain control over their own health, focussing on self-management and behaviour changes. Therefore, a 12-month follow-up is appropriate, since the process of behavior change will take at least 6 months [67].

A possible limitation to our study is the exclusion of patients who do not have sufficient understanding of the Dutch language. About 13% of the Dutch population are non-Western immigrants and their offspring. A proportion of them has insufficient command of the Dutch language; therefore, a part of the potential target population for this intervention will probably have to be excluded. Another limitation to our study is that blinding of patients, therapists, GPs and researchers to treatment allocation is not possible, due to the nature of the intervention.

In conclusion, if proven cost-effective, psychosomatic therapy would provide a valuable additional treatment option for adult patients with MUS.

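### Analyst blinding is ruled out because the analysts also collect data, but that reason does not prevent a masked analysis of the self-reported primary outcome

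*Protocol article*

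**What the plan says.** Allocation and blinding makes two separate statements. On patients and therapists: "Since psychosomatic therapy is a face-to-face intervention, patients and therapists cannot be blinded to allocation". On the analysis: "The data analysts will not be blinded to treatment assingments, as this would be unfeasible because they are also involved in data collection".

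The limitations paragraph of the Discussion gives another reason for a wider group: "blinding of patients, therapists, GPs and researchers to treatment allocation is not possible, due to the nature of the intervention".

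On the data themselves, Primary outcome says: "The PSFS is a self-reported, thoroughly validated, responsive measurement instrument for up to three individual activities". Data collection randomised trial says: "Data will be collected and stored digitally using Castor EDC", and "The participants will receive an e-mail with a link for all baseline and follow-up measurements, and if necessary, a reminder, to complete the measurements online". Where this brings no answer, "an independent research assistant will call them to encourage them to fill out the questionnaires". Data management adds that participants carry a code and that the principal investigator keeps the code list.

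**The concern.** Having an analyst who also collects data is a staffing choice. It explains why that person may know allocations. It does not explain why the model must be fitted by someone who knows them, or on a file that shows them. The face-to-face nature of the therapy, the reason given in the Discussion, accounts for unblinded patients and therapists but not for unblinded model fitting.

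At stake is the handling of the primary outcome in all 158 patients and of the other questionnaire scales. The people who report the outcome know their arm, and the trial has no data monitoring committee and no interim analysis; only internal audits are foreseen, and these may not happen (Recruitment of study participants). Any judgement left open at the analysis stage would, as the plan stands, be made with the arms in view.

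**Working it through.** No figure in the plan depends on analyst blinding, so the check is mainly a comparison of sections.

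**1. Sample size, for completeness.** Inputs from Sample size and power calculation: difference 1, SD 2, alpha 0.05 (taken as two-sided), power 0.80, dropout 20%.
- n per arm = 2 × (1.960 + 0.842)² × 2² / 1² = 62.8, rounded up to 63.
- 63 / 0.80 = 78.75, rounded up to 79 per arm, or 158 in total.

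This matches the plan. Masking the analyst changes none of these terms.

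**2. Does the stated reason block a masked analysis?**

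| Feature | What the article says | Consequence for masking |
|---|---|---|
| Primary outcome | Self-reported PSFS | No staff assessment to unblind |
| Entry | Online by the patient; paper allowed and also stored in Castor | Either form can sit in a recoded file |
| Identification | Participant codes; list held by the principal investigator | Codes can be replaced in an extract |
| Chasing non-responders | Independent research assistant | This task does not fall to the analyst |
| Model | Random intercept, other variables fixed, three time points | Needs an arm label, not its meaning |

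Nothing here makes a masked fit of the primary model infeasible. Arm labels alone would not be enough: an analyst who helped collect the data may recognise patients by study number, so the numbers must change too.

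**3. What cannot be masked this way?**
- Consultation counts come from the GP (Secondary outcomes), and GPs are told the allocation (Allocation and blinding).
- The GPE, SRS and WAI forms exist only in the intervention arm, as does the therapists' session registration (Process evaluation, Quantitative data).
- The iMCQ records care use, which could reveal therapy contacts.
- The per-protocol set is defined by at least four sessions (Statistical analysis), which identifies the arm.
- Range and entry-error checks run weekly during collection (Data collection randomised trial), before any extract exists.

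Masking is therefore available for the intention-to-treat analysis of the PSFS and the questionnaire scales, and not for the whole analysis.

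**4. Can the size be put in numbers?** Not from the document. One could compute the false-positive risk of choosing the better of the 4- and 12-month tests. It is 1 − 0.95² = 9.75% if they are independent, 9.1% at an assumed correlation of 0.5 and 7.0% at 0.9. But an analyst who sees only A and B could make the same choice, so these figures do not measure what masking would gain. Naming the time point in advance is what prevents that choice.

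**The case against.** The strongest reply is that this is a disclosed, minor preference. The dominant bias, unblinded patients rating themselves, stays whatever the analyst knows. Scoring rules, the imputation model and subgroup cut-points are commonly fixed in a statistical analysis plan; one may exist but is not shown, and it could leave an unblinded analyst little discretion. Multiple imputation is only a sensitivity analysis and the subgroups are exploratory. The plan also has safeguards: a masked randomisation sequence, an audit trail and programmed validation checks. All of this stands and limits the weight of the point. It does not rescue the stated reason, which is the article's own and does not support its conclusion.

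Four stronger readings are tempting, and the document does not support them.
- *All outcomes are self-completed.* The consultation count, which also appears in the power section, is reported by the GP.
- *The two sections contradict each other.* Their reasons differ, but one concerns data analysts and the other researchers in general, and both say that there is no blinding. No reader is misled about conduct.
- *The Discussion is wrong to list researchers as unblinded.* A research assistant sends out allocations and telephones intervention patients, and a team member interviews 15 to 30 of them (Qualitative data). That disclosure is true.
- *Bias has been introduced.* Only a risk is shown.

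**Conclusion.** The point holds in a limited form. The article rules out analyst blinding for a reason that does not prevent it for the self-reported primary outcome and the questionnaire scales. The consequence is an avoidable risk of bias of unknown size in an open-label, self-report trial. This is a cheap improvement, not a flaw that invalidates the analysis.

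The conclusion assumes that the team includes someone other than the model-fitter who can prepare an extract. The Steering Committee has two methodologists, but the article does not say whether they are the analysts, and they are not on the list of those with source-data access. It also assumes that the analyst does not go back to identified records in Castor while the model is being finalised. How much discretion remains depends on an analysis plan that is not shown.

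**What to change.** Replace the sentence on data analysts in Allocation and blinding with text to this effect:

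> Final scoring of the PSFS and the other questionnaire scales, and the intention-to-treat mixed models for them, will be run on an extract from Castor with new participant numbers and arms labelled A and B. A team member who does not run the models prepares the extract and holds the key. Therapy-session data, GPE, SRS, WAI, iMCQ and any other data that reveal the arm are held back until the output of the primary model is final. Per-protocol, cost and process analyses follow release of the key.

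In the Discussion, keep the statement that research staff who handle allocation, data collection and interviews are unblinded, and add that the primary model is fitted under masked labels. Say also that the weekly data checks and patient self-report remain unblinded.

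The cost is one re-keying step and later merging of arm-revealing data. A model-fitter with no part in data collection would be a stronger safeguard, if one is available. According to Trial status, recruitment was still under way at submission and follow-up was expected to end in January 2021, so the change could be made before analysis.

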## Methods: data collection, management and analysis

### Data collection

#### Data collection randomised trial

Data will be collected and stored digitally using Castor EDC [48]. Castor EDC is a Cloud-based Electronic Data Capture platform that enables easily capture of our data. Castor EDC is fully compliant with Good Clinical Practice, maintains stringent data security procedures and provides an audit trail. We will develop a case record form (electronic document designed to record all the information for an individual study subject), build a database, define a procedure for data entry, define and programme validation checks to ensure the consistency of the dataset, and set up the randomisation procedure, web questionnaire and/or logistic module. We will check for data-entry errors and range checks in values weekly to improve data quality during data collection. The participants will receive an e-mail with a link for all baseline and follow-up measurements, and if necessary, a reminder, to complete the measurements online. If participants still fail to respond, an independent research assistant will call them to encourage them to fill out the questionnaires. In case participants prefer a paper version, the measurements will be send by regular mail.

#### Data collection baseline demographic and clinical characteristics

Data will be obtained on patients’ baseline demographic and clinical characteristics by the first questionnaire. The questionnaire consists of questions about age, gender, marital status, socio-economic status (employment and level of education), source of income and working hours. The intensity, duration of the symptoms and interference with daily living, expectations about the prognosis of complaints and about the effect of the treatment will also be assessed in the first questionnaire. The number and severity of the symptoms will be measured with the PHQ-15 [28, 29] (at baseline and at 12 months).

### Data management

Data will be stored on Castor EDC. In case people prefer a paper version of the questionnaires, then the completed paper questionnaires will be stored in a locked closet at the Department of General Practice and Elderly Care Medicine of the VUmc. This data will also be stored on Castor EDC. Participants will be assigned with a code. The code list will be safeguarded by the principal investigator. The principal investigator, researcher, research assistants and coordinating investigator will be able to access the source data. Data will be kept for 15 years.

The audio recordings of all qualitative data will be stored securely in a safety Cloud and only accessible on a password-protected computer. All audio recordings will be destroyed immediately after processing.

### Statistical analysis

The primary data analysis will be performed according to the intention-to-treat principle (ITT) as outlined in the Consolidated Standards of Interventional Trials (CONSORT) Statement [49], i.e. all patients who were enrolled and randomly allocated to either group are included in the analysis and are analysed in the group to which they were randomised. We also will perform a per-protocol analysis. Data of patients in the intervention group who have completed at least four sessions will be used for the per-protocol analysis. Special care will be taken to gather follow-up data on all patients, regardless of whether they comply to the intervention that they are randomised to ,or not.

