**Fig. 1 Fig1:**
[figure not shown]
Schedule of enrolment, interventions and assessments. *PST* psychosomatic therapy; *CAU* care as usual; *PHQ-15* Patient Health Questionnaire 15-item somatic symptom scale; *PSFS* Patient Specific Functioning Scale; *iMCQ* iMTA Medical Consumption Questionnaire; *iPCQ* iMTA Productivity Cost Questionnaire; *NRS* numeric rating scale; *SF-36* Short Form Health Survey-36 items; *4DSQ* Four Dimensional Symptom Questionnaire; *GPE* Global Perceived Effect; *IAS* Illness Attitude Scale; *IPQ-B* Brief Illness Perception Questionnaire; *SRS-DV* Session Rating Scale Dutch version; *WAI-SF* Working Alliance Inventory short form; *1* only intervention group, directly after first session; *2* only intervention group directly after last session

We will perform a pragmatic randomised effectiveness trial with economic evaluation in primary care with patients aged 18–80 years who frequently, i.e. twice or more in the past months, consult their GP for MUS. Details regarding recruitment are presented below (see ‘Recruitment of study participants’ section). Patients will be individually randomised into intervention (psychosomatic therapy in addition to usual care) or control condition (usual care alone). The intervention (psychosomatic therapy) consists of 6 to 12 sessions, depending on number and severity of the patient’s symptoms, each of 30–45 min. Therapy will be delivered by a qualified psychosomatic therapist. The primary outcome measure will be functioning and disability measured with the Patient-Specific Functional Scale (PSFS) [24]. All patients will be followed for 1 year and will be asked to complete questionnaires at baseline and at 4 and 12 months’ follow-up. Participants in the intervention group will be referred to one of the 26 participating qualified psychosomatic therapists, physiotherapists or exercise therapists with a special interest in MUS, who receive a training for this study.

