#### Care as usual

Patients in the control group will receive usual care provided by the GP and other health care professionals, with no restrictions. The guideline on the management of MUS of the Dutch College of General Practitioners [30] describes the usual care. It recommends GPs to focus on the exploration of the symptoms, and on related cognitions, emotions and behaviour, and apply psychoeducation, monitoring, and, when necessary, to refer a patient to a physical therapist, a mental health nurse-practitioner or a psychologist.

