#### Economic evaluation

##### Cost-effectiveness of the intervention

We will conduct an economic evaluation from a societal perspective in accordance with the Dutch guidelines for economic evaluation [50]. Effectiveness is presented in terms of quality-adjusted life years (QALYs). QALYs are a combination of quality of life and survival, where quality of life is expressed as a utility score between 0 (representing death) and 1 (representing perfect health). Utility scores will be calculated through the SF-6D, which is a well-known classification for describing health derived from a selection of SF-36 items [36, 51]. Based on the SF-6D health state, each patient is assigned a utility score at three time points (baseline, 4 months, 12 months), using tariffs from the general population. QALYs will be calculated using the area-under-the-curve method, using the utility scores at baseline, 4 months and 12 months.

Since the economic evaluation will be performed over a time horizon of 1 year, costs and effects will not be discounted.

The cost analysis consists of two main parts. First, at patient level, volumes of care related to the care of patients with MUS will be measured by means of the iMCQ and iPCQ [41, 42]. The second part of the cost analysis consists of determining the cost prices for each volume of consumption. The standard cost prices from the ‘Dutch Guidelines for Cost Analyses’ [52] will be used to determine the cost prices for each volume of consumption. For units of care where no standard prices are available real cost prices will be determined. To obtain total costs, resource use will be multiplied with the cost prices. Productivity losses will be valued by means of the friction cost method [53–55].

Differences in costs and QALYs per patient between the two treatment arms will be calculated, according to the ITT and the per-protocol principle. Patients in the intervention group that have completed at least four sessions will be used for the per-protocol analysis. Where relevant, incremental cost-effectiveness ratios (ICERs) will be calculated to reflect the extra costs per QALY gained.

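### The supplementary per-protocol analyses select on session attendance in the intervention arm only, so their effect, cost and QALY estimates are open to selection bias of unknown size and direction

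*Protocol article*

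**What the plan says.** The Statistical analysis section of the protocol article makes ITT the primary analysis, with every randomised patient kept in the allocated group. It then adds: "We also will perform a per-protocol analysis". The set is defined in one sentence: "Data of patients in the intervention group who have completed at least four sessions will be used for the per-protocol analysis".

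The economic evaluation (Cost-effectiveness of the intervention) applies both principles: "Differences in costs and QALYs per patient between the two treatment arms will be calculated, according to the ITT and the per-protocol principle". It repeats the rule: "Patients in the intervention group that have completed at least four sessions will be used for the per-protocol analysis".

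Neither place gives a criterion for the usual-care arm, an adjustment for the selection, or an order of importance between the two cost-effectiveness results.

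Three other statements bear on the rule:

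- Study design: "The intervention (psychosomatic therapy) consists of 6 to 12 sessions", with the number tied to how many symptoms the patient has and how severe they are.
- Care as usual: "Patients in the control group will receive usual care provided by the GP and other health care professionals, with no restrictions".
- Discussion: "psychosomatic therapy is a well-accessible intervention already delivered in primary care by physical therapists with special interests in MUS".

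**The concern.** A per-protocol analysis is usually read as showing what the therapy does for those who take it. Here, patients who stop before the fourth session are removed from one arm, while the usual-care patients who would have behaved the same way stay in the other. If those who stop early would have fared differently in any case, that prognostic difference is counted as treatment effect.

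The rule also says nothing about controls who obtain psychosomatic therapy themselves, although their care is unrestricted and the therapy is available in ordinary practice.

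The economic analysis has a further problem. Dropping short courses removes the cheapest courses of therapy, so the mean therapy cost per intervention patient rises. The QALY difference is exposed to the same selection as the PSFS. Cost-effectiveness is a stated aim, and the two results are named side by side, so a reader could quote a non-randomised ICER as the equal of the randomised one.

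**Working it through.** **Inputs from the protocol (Sample size and power calculation; Allocation and blinding).** Relevant difference 1 PSFS point, SD 2, alpha 0.05 (taken as two-sided), power 0.80, dropout 20%, allocation 1:1, 79 patients per arm.

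**The plan's own figure.** n per arm = 2 × (1.96 + 0.84)² × 2² / 1² ≈ 62.8, rounded up to 63. Allowing for dropout, 63 / 0.80 = 78.75, rounded up to 79. The stated size reproduces.

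**Bias of a one-arm exclusion.** Let q be the share of the intervention arm with fewer than four sessions. Let g be the mean PSFS change in those with at least four sessions minus that in those with fewer, supposing the therapy has no effect. Write m for the mean change among those with at least four sessions.

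- Whole-arm mean = (1 − q) × m + q × (m − g) = m − q × g.
- With no true effect, the control mean equals the whole-arm mean.
- Per-protocol difference = m − (m − q × g) = q × g.

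**Assumed range.** The documents give neither q nor g. The false-positive rate below is for a two-sided normal test at 5% with SD 2, 79 × 0.8 = 63.2 controls and 63.2 × (1 − q) intervention patients. It approximates the planned mixed model.

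| q | g | Spurious difference (points) | False-positive rate |
|---|---|---|---|
| any | 0 | 0 | 0.050 |
| 10% | 0.5 | 0.05 | 0.052 |
| 20% | 1 | 0.20 | 0.083 |
| 20% | 2 | 0.40 | 0.185 |
| 30% | 1 | 0.30 | 0.119 |
| 30% | 2 | 0.60 | 0.334 |

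One row in full: for q = 20% and g = 1, SE = 2 × √(1/63.2 + 1/50.56) = 0.377 and the shift is 0.20 / 0.377 = 0.53. The rejection rate is P(Z > 1.43) + P(Z < −2.49) ≈ 0.083.

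A value of g = 2 is a full SD and should be read as an upper case. A negative g gives the same sizes with the sign reversed, against the therapy.

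**The alternative.** The complier average causal effect is the ITT difference divided by the difference between arms in the proportion receiving therapy. If the true ITT difference is zero, so is this estimand, whatever g is. The price is precision. The ITT standard error is 2 × √(2/63.2) = 0.356. With an assumed receipt of 80% against 0%, it becomes about 0.356 / 0.80 = 0.445, compared with 0.377 for the per-protocol comparison at q = 20%.

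**The case against.** ITT is primary, and the per-protocol analysis is an addition. Costs and QALYs are also analysed by ITT, which is named first, and the economic evaluation sits under the general Statistical analysis heading. Follow-up is sought from compliers and non-compliers alike. All of this stands. A reader might infer that the trial's main effect or cost-effectiveness result is biased; the documents do not support that.

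A reader might also take the bias as certain and in favour of the therapy. Neither follows. Session number is tied to symptom burden, so some short-course patients may be milder cases or may have improved early, and g could be zero or negative. In the cost analysis, removing the cheapest courses raises the therapy cost, which counts against the therapy.

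That every control is kept is inferred from silence, and a fuller protocol or analysis plan could state a control rule. This is fair, but it does not rescue the rule. No session-count criterion can be matched in an arm that is not assigned sessions, and the article states the one-arm rule twice.

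Use of the therapy by controls is possible, but no rate can be derived. The offer of therapy to controls after the study may reduce the incentive to seek it earlier.

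Four sessions against a planned 6 to 12 may look like a contradiction. It is not: one figure is a minimum exposure for an analysis set, the other the planned course. The relation between them is simply not explained.

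Finally, a complier analysis has its own weakness. With a four-session cut-off it assumes that one to three sessions do nothing, which is doubtful and would inflate the estimate. This objection stands and shapes the remedy.

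**Conclusion.** The point holds for the supplementary per-protocol estimates of effect, costs and QALYs, and only for those. As written, the rule conditions on an event after randomisation that exists in one arm, with no stated counterpart or adjustment.

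The resulting bias on the PSFS is q × g. Over the assumed values tabulated, it runs from zero to 0.6 points in either direction, against a relevant difference of 1; q = 20% with g = 1 gives 0.2. Both quantities are assumptions. The bias in costs and QALYs cannot be sized from the documents. ITT results are untouched, but the economic section should say explicitly that they take precedence.

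**What to change.** 1. Estimate the effect of receiving therapy as a complier average causal effect in all randomised patients, with allocation as the instrument. This can replace the per-protocol comparison or stand beside it.
2. Define receipt primarily as any psychosomatic therapy session, with the four-session definition as a sensitivity analysis. Take receipt from the therapists' session registration and, for controls, from the iMCQ or a GP report.
3. In the economic evaluation, state that ITT is the basis for the ICER and that any per-protocol cost-effectiveness result is supportive only.
4. Ask the investigators to explain how the four-session threshold relates to the planned 6 to 12 sessions.

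The cost is small: revised wording, one more model and possibly one added questionnaire item. Session registration and follow-up irrespective of compliance are already planned. The downsides are a wider interval, reliance on the assumption that allocation acts only through receipt of therapy, and less exact measurement of receipt in controls than in the intervention arm.
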